#### Power analysis

With the pre-specified number of sites (90) and design (Table 1; stepped-wedge design with 3 waves and 6 time periods; n = 432 TBC overall average scores), we investigated the PF intervention effect that is detectable with at least 80% power of a 2-sided significance test with α = 0.05. Power was calculated by simulating ten thousand datasets with modest correlation of TBC overall average scores over time (*r* = 0.35; ICC = 0.32) [57], and a standardized mean difference between control and PF conditions of *d* = 0.5 (i.e., a difference of half a standard deviation). Power was 0.92 to detect this effect with the planned number of sites. To allow for withdrawal of a small number of sites after baseline, we plan to enroll 90 practice sites (30 in each wave). Power for the secondary blood pressure outcome was also calculated by simulating ten thousand datasets. In all conditions, we assume an average of 150 patients with HTN per site and time period (i.e., 64,800 observations of patient BP over all sites and time periods). The intraclass correlation for BP control was specified as ICC = 0.85 based on an estimate from our previous EvidenceNOW study [25]. For the control condition, we specified a rate of BP control of 70%. For the PF condition, we specified an increase in the rate of BP control to 75%, and for the follow-up condition, we specified a decrease to 72%. The difference between the control and PF conditions corresponds to IRR = 1.07. Power to detect this IRR was > 0.99.

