### Study design

Using a stepped wedge randomized controlled trial (RCT) design, we randomly assign 90 practices to one of three waves (Table 1). Waves are separated by 6 months (i.e., a new wave enters the intervention phase every 6 months), and the intervention period lasts 12 months. Data collection for the primary outcome (i.e., adoption of TBC) occurs immediately prior to the beginning of the intervention period and at 12 months. BP control (i.e., secondary outcome) is measured every six months in all clusters at every time period so that each cluster provides data points in both the control and intervention conditions.

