#### Primary outcome

To measure our primary outcome (Table 4), adoption of TBC for improving adoption of HTN strategies, we adapted two instruments: the 29-item Primary Team Dynamics Survey Measure and a subscale from the Team Process Survey Measure. The Primary Team Dynamics Survey Measure is a validated instrument designed to measure team dynamics in primary care settings [46]. The 29-item instrument examines seven factors that map to four out of five elements of TBC: clear roles, shared goals, mutual trust, and effective communication. Respondents will be asked to rate their level of agreement on a scale from 1 (*Strongly disagree*) to 5 (*Strongly agree*) to statements related to TBC. Participants also complete the 5-item monitoring progress toward goals subscale of the team process measure. Respondents rate the extent to which their team participates in activities related to goal monitoring on a scale of 1 (*Not at all*) to 5 (*To a very great extent*). Practice staff in each wave complete the TBC Assessment Tool at baseline and 12- and 18-month period (end of intervention period). Both surveys were adapted to include language specifically related to HTN management. This allows us to measure the degree to which practice teams adopt TBC strategies for HTN management.

**Table 4 Tab4:** Measures and data source

	MEASURES	DATA SOURCE/COLLECTION
Primary Outcome	Adoption of team-based care for improving adoption of hypertension strategies (TBC) [46]	Provider and staff survey Baseline & 12 months
Secondary Outcomes:	Clinical outcome: BP control defined as proportion of patients with HTN who achieve BP < 140/90 (NCQA HEDIS)	EHR every 6 months for 12 months
Implementations outcomes	Fidelity: Practice facilitation [47]	Salesforce tracking system PF interviews
	Sustainability of TBC for implementing HTN management strategies and BP outcome	Provider and staff survey at 18 months EHR data at 18 months
Practice Context	Organizational readiness [39] Barriers and facilitators Staffing, financial resources Staff and provider burnout and job satisfaction	Provider and staff survey baseline and 12 months Qualitative interviews 12 months

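### The 0.92 power for the primary outcome needs a TBC score from each practice every six months; the stated schedule takes two or three per practice and gives power of about 0.4 to 0.6

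*Protocol article*

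**What the plan says.** The Power analysis section sets the simulation for the primary outcome as a "stepped-wedge design with 3 waves and 6 time periods; n = 432 TBC overall average scores", with a standardised difference of 0.5, a correlation over time of 0.35 and an ICC of 0.32. It concludes: "Power was 0.92 to detect this effect with the planned number of sites". The target was "at least 80% power of a 2-sided significance test with α = 0.05".

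The collection schedule is given elsewhere. Under Study design: "Data collection for the primary outcome (i.e., adoption of TBC) occurs immediately prior to the beginning of the intervention period and at 12 months". The next sentence of that section reserves measurement in all clusters at every period for blood pressure. The Abstract and Table 4 also place the primary outcome at baseline and 12 months. Under Primary outcome: "Practice staff in each wave complete the TBC Assessment Tool at baseline and 12- and 18-month period". The 18-month score serves the sustainability outcome.

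The Quantitative analysis section specifies a linear mixed model with a random site effect and fixed effects for time and condition. It does not say whether time enters as separate periods or as a linear trend.

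**The concern.** Two or three scores from each of 90 practices cannot total 432. The power calculation appears to have given the primary outcome the six-monthly schedule that the protocol reserves for blood pressure.

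More than the number of scores is at stake. Because each wave is surveyed relative to its own start, control and facilitation scores hardly overlap in calendar time. Once time is in the model, most of the before-after change within practices cannot be separated from a time trend. A true half-standard-deviation effect could then be missed about as often as it is found, while readers are told that the chance of finding it is 92%. A practice in wave 2 or 3 that withdraws while waiting would also contribute no TBC score at all.

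**Working it through.** **Inputs.** From Power analysis: d = 0.5, two-sided α = 0.05, ICC 0.32 (r = 0.35), 90 practices, 30 per wave, 6 periods. From Study design: waves six months apart, intervention lasting 12 months. From Quantitative analysis: random site, fixed time, fixed condition. The moderator paragraph gives condition three levels (control, facilitation, sustainability). Total variance is set to 1.

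**Number of scores.**
- 432 / 6 = 72 practices, or 24 per wave. Ninety practices would give 90 × 6 = 540.
- The blood pressure calculation in the same section has the same base: 64,800 / 150 = 432 site-periods.
- Stated schedule: 90 × 2 = 180 scores, or 90 × 3 = 270 with the 18-month survey.

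**Formula.** Power = Φ(0.5/SE − 1.96), where SE is the generalised least squares standard error of the facilitation-versus-control coefficient. Detectable d at 80% power = (1.960 + 0.842) × SE.

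**The article's figure first.** Six scores per practice, 24 practices per wave, linear time:
- ICC 0.35: SE = 0.149, power 0.92.
- ICC 0.32: SE = 0.151, power 0.91.
- A mixed-model simulation (600 datasets, ICC 0.32) also gave 0.92.
- With separate period effects: 0.86 to 0.87.

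The stated 0.92 is thus reproduced on a six-period layout.

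**The stated schedule in calendar months.**

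| Wave | Control score | Facilitation score | Sustainability score |
|---|---|---|---|
| 1 | 0 | 12 | 18 |
| 2 | 6 | 18 | 24 |
| 3 | 12 | 24 | 30 |

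Only month 12 has both a control score (wave 3) and a facilitation score (wave 1). With separate period effects, the control scores at months 0 and 6 come from one wave each and are absorbed by their own period effects. The 18-month scores do not help while sustainability is its own level. What remains is wave 1 against wave 3 at month 12, so SE = √(1/n + 1/n), whatever the ICC:
- n = 30: √(2/30) = 0.258; 0.5/0.258 − 1.96 = −0.02; power 0.49.
- n = 24: √(2/24) = 0.289; 0.5/0.289 − 1.96 = −0.23; power 0.41.

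A linear time trend recovers some information, but only by assuming that the trend is straight:

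| Practices | Scores each | SE (linear time) | Power |
|---|---|---|---|
| 90 | 2 | 0.243 to 0.244 | 0.54 |
| 90 | 3 | 0.227 to 0.229 | 0.59 to 0.60 |
| 72 | 2 | 0.272 to 0.273 | 0.45 |
| 72 | 3 | 0.254 to 0.256 | 0.50 |

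**Detectable effect, 90 practices.** Period effects: 2.802 × 0.258 = 0.72. Linear time: 2.802 × 0.243 = 0.68 with two scores and 2.802 × 0.228 = 0.64 with three.

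**The case against.** **432 need not be 72 × 6.** If each wave is followed only to its own 18 months, there are 4 + 5 + 6 = 15 wave-periods, or 450 site-periods with 30 practices per wave. A 5% loss after baseline gives 90 + 0.95 × 360 = 432. That suits the wording "To allow for withdrawal of a small number of sites after baseline" better than a 20% loss, and it also gives power of about 0.91 with linear time. This stands: the layout cannot be identified for certain, and the 72-practice figures rest on a loss rate that the article does not state. But this reading also needs a TBC score every six months, so the mismatch remains.

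**Table 1 is not visible.** Its caption says it marks TBC collection, so an extra month-0 survey of waves 2 and 3 cannot be excluded. With one, 90 practices give 0.53 to 0.54 (period effects) or 0.67 to 0.68 (linear time), and just under 0.70 if facilitation and sustainability are also pooled. The text in four places gives no such survey.

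**Other models are possible.** Pooling facilitation with sustainability on the stated schedule gives at most 0.64. Predictive covariates, which the article allows, could reduce variance by an amount it does not give. Dropping time restores 0.95 or more, but the analysis model includes time, and without it the test is an uncontrolled before-after comparison. No layout with two or three scores per practice and time in the model reached 0.80.

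**A null result would still carry information.** The article promises 95% confidence intervals. This is fair, but those intervals would be much wider than the stated power implies.

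**Conclusion.** The concern holds. The power claim for the primary outcome is wrong as written, because it rests on scores that the protocol does not plan to collect. For d = 0.5 with 90 practices, power on the stated schedule is 0.49 (period effects) to 0.60 (linear time, three scores); with 72 practices it is 0.41 to 0.50. The smallest effect detectable with 80% power at 90 practices is about 0.64 to 0.72 standard deviations.

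These figures assume d on the total standard deviation, ICC 0.32 to 0.35, a random site intercept, sustainability as its own condition level and no gain from covariates. The range covers both forms of the time effect because the article does not choose one. The more favourable alternatives raise the top of the range to about 0.70, still short of the 80% target.

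**What to change.** 1. In Power analysis, delete n = 432 and the 0.92. State the TBC collection times used, the form of the time effect and the assumed loss of practices, then give the recomputed power. On the assumptions above this is 0.49 to 0.60 for d = 0.5 with 90 practices, with a detectable d of 0.64 to 0.72.
2. Make Study design, Primary outcome, Table 1, Table 4 and Power analysis agree on how many TBC scores each practice gives and when.

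This is a text correction plus a rerun of the existing simulation. Its only cost is a less favourable figure.

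Surveying every practice at each six-month period would bring the data up to the power calculation: 0.92 to 0.96 with 90 practices, if the facilitation effect is constant from month 6. That is a design trade-off, since it adds response burden in small practices and a risk of non-response. The correction above does not depend on it.

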#### Fidelity analysis

We will calculate adherence to the PF protocol as the number of components fully or partially implemented divided by the total number of possible components [58]. We will assess visit dose (i.e., number of visits completed, type of visit conducted (in person vs. remote), and length of visit). We will compare pre and post-intervention HTN checklist responses to changes in the number of evidenced-based HTN strategies implemented at each practice.

#### Qualitative analysis

Interviews are transcribed verbatim and imported into Atlas.ti for analysis. The study uses an abductive content analysis that systematically integrates practices from inductive analysis (e.g., grounded theory) [59] and deductive analysis (i.e., applying codes associated with the guiding framework [CFIR]), while remaining open to informative deviations from those frameworks. Coding begins with an independent reading of the transcripts to identify preliminary themes, relevant patterns, and generative questions, followed by focused coding to identify clustered concepts, organize ideas, identify major emergent themes, and link them to relevant theoretical constructs. Throughout, coders will meet to review their coding, conduct team debriefing meetings, and reach a consensus on code names and meanings [60]. Once all transcripts are collaboratively coded, analytic domains are identified, and major and minor thematic areas described. Two coders independently code at least 10 interviews to establish the inter-rater reliability (IRR) and if it is inadequate (Krippendorff’s alpha < 0.80) [61], the lead investigators will work collaboratively to refine and/or clarify the coding scheme and provide additional coder training. The research team refines and/or clarifies the coding scheme and provides additional coder training. Double coding continues until adequate IRR is achieved.

#### Data integration

The analysis integrates the qualitative and quantitative data in a nested, parallel mixed-methods design [62–64]. Each interview is linked to descriptors of the originating study site’s characteristics, including potential moderators, mediators, and outcomes. These descriptors are used during analysis to categorize and interpret qualitative data in Atlas.ti using group functions. We triangulate findings from the baseline assessment, 12, and 18, -month adoption and sustainability data waves by developing a thematic matrix that includes practice and team-level characteristics and compare side-by-side those factors that were identified as facilitating or hindering the introduction, adoption, and sustainability of TBC for HTN strategies. This analysis examines how themes emerging from the qualitative data converge with, contextualize, explain, or expand the quantitative findings.

## Discussion

PF is a promising strategy to support the effective implementation of TBC in SIPs, but is understudied in small practices that serve immigrant and minority populations that are experiencing significant disparities in CVD-related health outcomes [65–67]. This study begins to fill this gap by leveraging BEHS’ unique, large network of urban small practices to test the hypothesis that PF can increase TBC, even in the context of resource constraints, to improve HTN outcomes. Of note, the investigative team and BEHS are using a pragmatic design that is aligned with BEHS’ and practice’s preferences that all practices will receive the intervention over time. The study further addresses the lack of theory-driven analyses by applying organizational theory to explore the mechanisms by which PFs impact organizational readiness and adoption of TBC and clinical outcomes.

An additional strength of the study is the partnership between NYU investigators and the NYC Department of Health and Mental Health’s practice network, a group of practices that serve primarily, low-income, minority, and immigrant populations. Embedding research in their PF program, BEHS increases the potential for sustainable changes.

Potential limitations may include the potential for practices dropping out of the study, lack of fidelity due to intervention adaptions, and non-response bias. Additionally, we anticipate that facilitators may experience challenges in meeting with staff due to high patient volume or staffing turnover. However, the BEHS has long-standing relationships with their network practices and providers have noted the advantage of the PF process which facilitates engagement [18, 68]. If we encounter lower than expected responses, practice facilitators will conduct in-person and phone outreach to increase rates of engagement. Also, facilitators will receive training and ongoing supervision to support the intervention and engagement process. We are using a rigorous process to assess fidelity.

Despite the potential limitations, this study provides much-needed guidance on how to optimize the adoption and sustainability of TBC in independent primary care settings to reduce the burden of disease related to suboptimal BP control and address current gaps in prior research [20].

## Data Availability

The datasets generated and/or analyzed during the current study, including the PF Toolkit and all survey instruments, are not publicly available because of its use of information regarding private business operations, but will be made from the corresponding author on reasonable request. The details of data management procedures will also be made available by the corresponding author.

## Abbreviations

BEHS: Bureau of Equitable Health Systems
BP: Blood Pressure
CBPR: Community-Based Participatory Research
CFIR: Consolidated Framework for Implementation Research
CVD: Cardiovascular Disease
DOHMH: Department of Health and Mental Hygiene
EHR: Electronic Health Record
FTE: Full-time Equivalent
NCQA: National Committee for Quality Assurance
HHTeams: Healthy Hearts Teams
HTN: Hypertension
IRR: Inter-Rater Reliability
MOU: Memorandum of Understanding
OCRBS: Organizational Change Recipients’ Beliefs Scale
PCTGA: Primary Care Team Guide Assessment
PDSA: Plan-Do-Study-Act
PF: Practice Facilitation
QA: Quality Assurance
QI: Quality Improvement
QC: Quality Control
RCA: Root Cause Analysis
RCT: Randomized Controlled Trial
REACH: Regional Electronic Adoption Center for Health
SEM: Structural Equation Models
SIPs: Small Independent Primary Care Practices
TBC: Team-Based Care
